## Abstract

**Background:**

Temporomandibular disorders are a group of orofacial pain conditions that are commonly identified in the general population. Like many other chronic pain conditions, they can be associated with anxiety/depression, which can be related to changes in the activity of the dorsolateral prefrontal cortex. Some studies have demonstrated clinical improvement in subjects with chronic pain who are given therapeutic neuromodulation. Transcranial direct current stimulation is a noninvasive brain stimulation technique that allows the modulation of neuronal membranes. This therapy can enhance or inhibit action potential generation in cortical neurons. In some instances, medications acting in the central nervous system may be helpful despite their adverse side effects. It is important to determine if cathodal transcranial direct current stimulation over the dorsolateral prefrontal cortex, an area that modulates emotion and motor cortex excitability, has an analgesic effect on chronic temporomandibular disorders pain.

**Method/design:**

The investigators will run a randomized, controlled crossover double blind study with 15 chronic muscular temporomandibular disorder subjects. Each subject will undergo active (1 mA and 2 mA) and sham transcranial direct current stimulation. Inclusion criteria will be determined by the Research Diagnostic Criteria for Temporomandibular Disorders questionnaire, with subjects who have a pain visual analogic scale score of greater than 4/10 and whose pain has been present for the previous 6 months, and with a State-Trait Anxiety Inventory score of more than 42. The influence of transcranial direct current stimulation will be assessed through a visual analogic scale, quantitative sensory testing, quantitative electroencephalogram, and the State-Trait Anxiety Inventory score.

**Discussion:**

Some studies have demonstrated a strong association between anxiety/depression and chronic pain, where one may be the cause of the other. This is especially true in chronic temporomandibular disorders, and breaking this cycle may have an effect over the symptoms and associated dysfunction. We believe that by inhibiting activity of the dorsolateral prefrontal cortex though cathodal transcranial direct current stimulation, there may be a change in both anxiety/depression and pain level. Transcranial direct current stimulation may emerge as a new tool to be considered for managing these patients. We envision that the information obtained from this study will provide a better understanding of the management of chronic temporomandibular disorders.

**Trial registration:**

This trial was registered at clinicaltrials.gov on 24 May 2014 (Identifier: NCT02152267).

## Background

Pain is among the most common complaints reported by patients seeking care in a hospital setting or in a primary care unit. Patients with pain due to temporomandibular disorders (TMD), which are musculoskeletal disorders of the masticatory structures, are very common in the general population. Temporomandibular and craniofacial disorders are so prevalent that the International Headache Society has developed a classification for the many different types of head pain. The third edition of the International Classification of Headache Disorders was published in 2013 [1].

There are several strategies used to manage patients with TMD. Since there are many types of TMD, it is critical that clinicians make the proper diagnosis so that appropriate treatment is selected. Treatment strategies range from patient education and self-management to dental procedures and surgery. The most common symptom associated with TMD is muscle pain, which is often managed by cognitive awareness, behavioral changes, and stress management [2].

A study using functional brain imaging showed that, although the majority of temporomandibular disorders are associated with muscle pain, as they become chronic they are likely to have a centralnervous system (CNS) component [3]. Supporting this concept are behavioral studies that have demonstrated that TMD is often associated with psychopathology [4, 5].

It is now commonly accepted that chronic pain involves significant modifications in central neuronal excitability. In a fibromyalgia study using transcranial magnetic stimulation (TMS), the authors found higher thresholds in both sides of the resting motor cortex with lower up regulation responses. Furthermore, they found lower intracortical facilitation and inhibition. The effects of neural modulation to manage chronic pain are presently being studied [6].

Transcranial direct current stimulation (tDCS) modulates neuronal membranes of cortical neurons, enhancing or inhibiting their action potentials. Experimental animal studies have shown that anodal stimulation depolarizes the nerve membrane, which results in a long-term potentiation in the stimulated area [7, 8]. Some studies have shown pain reduction in subjects with fibromyalgia and chronic pain using neuromodulation [9–13]. Some suggest that anodal stimulation over the motor cortex decreases pain intensity by modulating the activity in the neuronal networks responsible for pain. Another study that evaluated the role of the thalamic ventral caudal nucleus in nociception, suggested a decrease of thalamic pain control output capacity in chronic pain patients [14]. Transcranial direct current stimulation may facilitate the descending inhibition of pain; however, the current evidence is weak [15].

Others studied the effects when transcranial direct current stimulation (tDCS) is placed over the dorsolateral prefrontal cortex (DLPFC) [16]. This area is involved with anxiety and depression without direct analgesic effect. Although not the objective, the authors found anxiety modulation after tDCS application over the DLPFC, when the cathode was placed over the right side (F4) and the anode on the left side (F3). These results show weak evidence of tDCS effects on anxiety, but they do suggest the need for additional investigation [16]. The modulation of DLPFC may also have analgesic effects through its excitatory interaction with the primary motor cortex [17].

If cathodaltDCS over the DLPFC has an analgesic effect through modulation of negative emotions, another important issue is to determine the best stimulation intensity to achieve this goal. Previous tDCS studies have used 1 or 2 mA, with 2 mA being more common. There is discussion regarding which intensity is more appropriate with cathodal tDCS. Some authors found that either 2 mA cathodal or anodal stimulation led to increased excitability of the primary motor cortex, whereas 1 mA stimulation had a specific effect, with cathodal current decreasing cortical excitability [18].

An advantage of tDCS is that it has minimal side effects. The most common adverse effects are itching, tingling, and mild headache that resolve just after the stimuli is terminated. These adverse effects depend on the intensity and duration of the treatment session. The most common protocols use a lower intensity (1 or 2 mA) with a treatment session duration of 20 or 30 minutes. To access tolerability and safety of tDCS, a side effect questionnaire has been developed [19].

## Aims

The main objective of this study is to investigate whether cathodal tDCS over the right DLPFC has analgesic effects in subjects with muscular TMD pain. This study will: (1) evaluate the tDCS effect on pain perception and pressure threshold; (2) evaluate whether tDCS has any effect on modifying anxiety and stress; (3) evaluate whether an EEG’s waves change from pre- to post-tDCS; (4) investigate whether there is an association of pain intensity with anxiety and EEG data pre- and post-tDCS; (5) compare the effects of 1 mA and 2 mA over pain intensity, anxiety, stress, and EEG.

## Methods

### Study design

This is a randomized, controlled crossover double blind study with one group undergoing three different interventions. Treatment order will be determined randomly. The CONSORT guidelines from 2010 to clinical trials will be used to guide the procedures [20].

### Eligibility criteria

To be included in this study, subjects must: (1) provide informed consent to participate in the study; (2) be between 18–60 years old, regardless of gender; (3) have a diagnosis of muscular TMD pain according to IA and IB, Axis I of Research Diagnostic Criteria for Temporomandibular Disorders (RDC/TMD); (4) have a visual analog scale (VAS) pain score of 4 or greater, present regularly for 6 months or longer; (5) have a State-Trait Anxiety Inventory (STAI) score of more than 42.

Subjects will be excluded from this study if they (1) are pregnant; (2) have contraindications to tDCS, such as metal implants on the head or implanted brain devices; (3) have a history of alcohol or drug abuse within the past 6 months as self-reported; (4) have used carbamazepine within the past 6 months as self-reported; (5) have a history of epilepsy, stroke, moderate-to-severe traumatic brain injury, or severe migraines; (6) have a history of neurosurgery as self-reported; (7) have a history of temporomandibular joint problems such as disc displacement, arthralgia, osteoarthritis, or osteoarthrosis (Axes I, II, and III diagnosis from RDC/TMD); (8) have a major psychiatric disorder such as schizophrenia or bipolar disorder; (9) have had any other previously diagnosed disorder that has pain symptoms similar to muscle TMD, such as fibromyalgia.

### Intervention groups

Each subject will be tested to determine the effect of cathodal tDCS over the DLPFC on anxiety using two different currents, 1 mA and 2 mA.

### Intervention A

This intervention will involve 1 mA tDCS, cathodal over the right DLPFC (F4). The anode will be placed over the contralateral supraorbital area (Fp1). Stimulation will be applied over a 20-minute period.

### Intervention B

This intervention will use the same parameters as intervention A, but using 2 mA.

### Intervention C

This will be the sham intervention. Stimulation electrodes will be placed at the same areas as for interventions A and B, but the current will be applied only for the first 30 seconds, after which it will be reduced gradually until it reaches zero. This method has been shown to be effective in previous studies [21].

In all the intervention groups, tDCS will be applied using 35 cm^2^ (5×7 cm) sponge electrodes soaked in saline solution (140mMolNaCl, water dissolved in Mille-Q). Anodal and cathodal electrodes will be connected in the tDCSdevice (Soterix Medical 1 × 1 tDCS 1300A, USA). Two 9-V batteries will deliver current.

All subjects will receive only one stimulation session for each type of intervention (IA, IB and IC), for a total of three sessions. After each tDCS session, the subject will complete a questionnaire to record any adverse affects. A trained researcher ([name]) will perform each procedure. One researcher who is responsible for the general supervision ([name]) during testing will hold the randomization list, and only the clinician responsible for the tDCS stimulation will know which intervention group is being applied. All clinical and neurological assessments will be performed at the Functional Electrostimulation Laboratory at Federal University of Bahia (Salvador, Brazil).

As this is a crossover study with only four weekly sessions, we believe that there will not be a compliance problem. Furthermore, since side effects are minimal, there is a low risk of dropouts due to this reason.

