**Fig. 1 Fig1:**
[figure not shown]
Flow of study procedures

**Table 1 Tab1:** Visit summary

	V1	V2	V3	V4
	Baseline/consent	1^st^ session	2^nd^ session	3^rd^ session
Consent form	X			
RDC/TMD	X			
VAS pain diary	X	X	X	X
VAS pain (pre-tDCS)		X	X	X
Sensory testing (pre-tDCS)		X	X	X
EEG recording (pre-tDCS)		X	X	X
tDCS stimulation (IA, IB, or IC)		X	X	X
Adverse effects questionnaire		X	X	X
VAS pain (post-tDCS)		X	X	X
ISTA	X	X	X	X
EEG recording (post-tDCS)		X	X	X
Sensory testing (post-tDCS)		X	X	X
*Approx. time*	*1 hour*	*3 hours*	*3 hours*	*3 hours*

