### Safety monitoring

At each stimulation session, subjects will complete a questionnaire to evaluate potential adverse effects of tDCS (tingling, burning sensation, headache, neck pain, mood alterations) on a 5-point scale. Subjects will be asked whether they experienced any side effects in an open-ended manner, and they will be specifically asked about headache, neck pain, scalp pain, burning sensations, tingling, skin redness, sleepiness, trouble concentrating, and acute mood change.

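### Adverse effects are recorded only after stimulation, so rates of headache, neck pain and other non-specific symptoms cannot be read as treatment-emergent

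*Protocol article*

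**What the plan says.** Under Intervention C the protocol article states: "After each tDCS session, the subject will complete a questionnaire to record any adverse affects". In Table 1 (Participant timeline) the instrument has a single row, "Adverse effects questionnaire", marked at V2, V3 and V4, listed below the stimulation row and absent at V1. The same table splits VAS pain, sensory testing and EEG into separate rows before and after tDCS.

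Safety monitoring says that at each session "subjects will complete a questionnaire to evaluate potential adverse effects of tDCS (tingling, burning sensation, headache, neck pain, mood alterations) on a 5-point scale". It adds an open question about side effects and a prompted list, under which "they will be specifically asked about headache, neck pain, scalp pain, burning sensations, tingling, skin redness, sleepiness, trouble concentrating, and acute mood change". It does not say what the five points grade, and it mentions no rating before stimulation.

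Under Eligibility criteria, patients must "have a visual analog scale (VAS) pain score of 4 or greater, present regularly for 6 months or longer" and "have a State-Trait Anxiety Inventory (STAI) score of more than 42". Severe migraines are excluded, as are fibromyalgia and other diagnosed disorders with similar pain, joint disorders and major psychiatric illness. Ordinary headache and neck pain are not. Each patient also has a sham session, and the questionnaire is completed at all three sessions.

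**The concern.** Several prompted items are symptoms these patients may already have on arrival: headache, pain in the neck or scalp, sleepiness, poor concentration. The Background section itself names mild headache among the commonest effects of tDCS and places temporomandibular disorders within head pain classification. One important safety item is thus also a plausible presenting complaint.

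With a single reading after stimulation, a patient who arrives and leaves with the same headache can give the same answer as one whose headache began during the session. Table 1 also lists sensory testing, which is taken to pain threshold at a tender masseter point, among the procedures before stimulation. Discomfort from that testing cannot be separated either.

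At stake is the reading of the tolerability record. The Background section says adverse effects depend on intensity, the trial compares 1 mA with 2 mA, and the article describes the treatment as having minimal adverse effects. Rates that include background symptoms can neither confirm nor refute that description.

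**Working it through.** The documents give no adverse-effect rate, test or power figure, so there is no stated number to reproduce. The check asks what a reading taken only after stimulation does to two possible summaries.

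**Inputs.** From the documents: 15 patients (Sample size), a sham and two active sessions per patient, and one questionnaire per session after stimulation. Assumed, because the documents give neither:
- p, the share of patients who arrive with a given symptom
- q, the share in whom stimulation induces it, independent of p

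It is also assumed that a patient who arrives with the symptom reports it afterwards.

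**1. Items summarised as present or absent**

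Recorded rate = 1 - (1-p)(1-q). With a sham that induces nothing, the sham rate is p, and the recorded risk difference is 1 - (1-p)(1-q) - p = (1-p)q. For q = 20 %:

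| p | Sham rate | Active rate | Recorded difference | True difference | Sham patients positive, of 15 |
|---|---|---|---|---|---|
| 20 % | 20 % | 1 - 0.8 × 0.8 = 36 % | 16 points | 20 points | 3 |
| 40 % | 40 % | 1 - 0.6 × 0.8 = 52 % | 12 points | 20 points | 6 |
| 60 % | 60 % | 1 - 0.4 × 0.8 = 68 % | 8 points | 20 points | 9 |

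If sham also induces symptoms, the same factor applies: difference = (1-p)(q_active - q_sham). With assumed induced rates of 0.30 and 0.10 and p = 0.3:
- active: 1 - 0.7 × 0.7 = 0.51
- sham: 1 - 0.7 × 0.9 = 0.37
- risk difference: 0.14 instead of 0.20
- risk ratio: 0.51/0.37 = 1.38 instead of 3.0

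**2. Items analysed as a mean score, within patient, against sham**

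Let the score after stimulation be background plus effect plus error, with assumed mean effects of 0.6 (active) and 0.2 (sham). A stable background is the same in both sessions and cancels, so the expected difference is 0.6 - 0.2 = 0.40 with or without a pre-stimulation reading. Only the standard error changes. With an assumed error SD of 0.5, a visit-to-visit background SD of w and 15 patients:
- post-stimulation score only: SE = √[2(w² + 0.25)/15], which is 0.18, 0.26 and 0.41 for w = 0, 0.5 and 1.0
- change from the pre-stimulation reading: SE = √[2(0.25 + 0.25)/15] = 0.26 for every w

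On this summary a pre-stimulation reading removes no bias. It improves precision only when background symptoms vary appreciably between visits, and loses some when they do not vary.

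**3. Item by item**

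Tingling, burning and skin redness are specific to the procedure, so p should be near zero and the factor near 1. Acute mood change is worded as a change. The problem therefore sits with headache, neck pain, scalp pain, sleepiness and trouble concentrating.

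**The case against.** The strongest reply is that the article contains no counting rule. A reader might infer that every symptom ticked after a session is counted as a tDCS effect. The text does not say so: Safety monitoring speaks of potential adverse effects and asks about side effects, and the 5-point scale might grade relatedness. The form itself is not shown, and a condensed article may leave item wording and derivation rules to fuller documents. This stands, so the claim has to be that background and induced symptoms cannot be separated, not that they are misattributed. It does not dispose of the point, because the visit schedule is shown, it separates before from after where it means to, and it places this instrument once. A relatedness grade would then rest on the patient's recall and judgement.

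A reader might also infer that the active-sham comparison is necessarily diluted. That does not follow. Dilution needs a present/absent summary, or scores near the top of the scale, and the article prescribes no dichotomy. The within-patient sham session is a real safeguard for mean scores.

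Three further points hold:
- Adverse effects do not appear in Aims, Outcomes, Study variables or Statistical methods, so no active-sham safety analysis is promised.
- The exclusions go beyond severe migraine and remove some background pain and mood symptoms.
- Data collection procedure has pain and anxiety measured before and after stimulation, which gives some context, though not for headache, neck pain, sleepiness or concentration individually.

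**Conclusion.** The point holds in limited form. No symptom checklist is planned before stimulation, so rates of the non-specific items cannot be read as treatment-emergent under sham, 1 mA or 2 mA. If items are reported as present or absent, rates are too high in all three conditions and the risk difference against sham is multiplied by (1-p): a true 20-point excess becomes 16 to 8 points for p from 20 % to 60 %. Those values of p and q are illustrations, and they rest on independence and on full reporting of symptoms already present.

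The documents do not support going further: they set no rule that attributes all symptoms to tDCS, and a stable background does not bias mean within-patient score differences. The primary outcome and the sample size are untouched. This is a modest but worthwhile improvement to the safety record.

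**What to change.** In Table 1 and Safety monitoring, split the adverse effects questionnaire into two rows. Patients would complete the same items on the same 5-point scale before stimulation at V2, V3 and V4, and again afterwards. The first reading is best taken just before the current starts, after the pre-tDCS sensory testing and EEG, so that it also captures discomfort from those procedures.

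Report items that are new or at least one point worse than that session's own pre-stimulation rating, by condition and within patient. The worsening part matters: counting only new symptoms over all 15 patients would correct the inflated rates but leave the (1-p) factor in the risk difference. Chance worsening will still occur, and the sham session shows how much.

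The cost is a few minutes of self-report at three visits of about 3 hours each, plus one derivation rule, with no extra staff. Listing symptoms beforehand may slightly raise expectation, equally in all three conditions.

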### Outcomes

The primary outcome of this study will be the extent to which this method will change baseline pain intensity (VAS). The subjects will record their experience on a daily basis in a pain diary. A weekly response average will be calculated before the first intervention and after each session. The averages will be used to compare the VAS values before and after each intervention. A decrease of 50 % will be considered a satisfactory clinical improvement.

Secondary outcomes will be the degree of change from baseline in power density of alpha and theta EEG bands. Other outcome measures will be pain pressure threshold (PPT), mechanical pain thresholds (MPTs), and STAI. Increase in PPT and mechanical thresholds indicate an improvement in subject pain condition; a decrease in STAI indicates a better emotional state.

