### Data collection procedure

After COAT institutional authorization, subjects will be contacted by phone to ascertain their interest. All interested participants will complete a pre-screening questionnaire. Each subject will be scheduled for an appointment in order to further determine if they meet the inclusion criteria. If they do, they will sign an informed consent and be formerly enrolled in the study.

Women of childbearing age will be required to take a urine pregnancy test during the screening process. If a subject becomes pregnant during the course of the study, she will be withdrawn. During this initial appointment, the subject will be asked to complete a daily pain VAS diary for 7 days. The average VAS score from this data will be used as a baseline pain value.

During a second visit (T2) all clinical and neurological assessments will be performed before and after the tDCS stimulation. The clinical assessments will be measured by VAS pain scores, anxiety measures, and quantitative sensory tests. Neurophysiological assessment will be measured by using an EEG to analyze cortical activity. Each patient will be clinically and neurologically assessed before and after the treatment session resulting in six data collection points (T2 to T7).

All subjects will be treated during a single session for three different interventions (IA, IB,or IC) with a washout period of 7 days between treatments in order to avoid any residual effects. As reported earlier, a single tDCS session usually is able to modify cortical excitability for 1 hour after stimulation [22, 23].

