### Technical and scientific resources

The two important goals of this research are to establish the most effective protocol for tDCS and to demonstrate a therapy that may be useful for TMD patients. The use of tDCS for TMD is feasible in clinical practices that have many patients presenting with this disorder. tDCS is noninvasive, low cost, and easy and rapid to implement. Further, this treatment has minimal adverse effects.

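### Adverse effects are collected only on stimulation days, after that day's stimulation, and not after the third session, so delayed effects may be missed or credited to the wrong intervention

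*Protocol article*

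**What the plan says.** Three places in the protocol article set the timing.

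- Intervention C: "After each tDCS session, the subject will complete a questionnaire to record any adverse affects".
- Safety monitoring: "At each stimulation session, subjects will complete a questionnaire to evaluate potential adverse effects of tDCS". The same section adds: "Subjects will be asked whether they experienced any side effects in an open-ended manner". It then lists symptoms to be prompted for, among them headache, neck pain, skin redness, sleepiness, difficulty concentrating and acute mood change. No recall period is given.
- Table 1 (Participant timeline): the row "Adverse effects questionnaire" is marked at V2, V3 and V4. It stands after the stimulation row and before the post-stimulation VAS row. V4, the third session, is the last visit shown.

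Between visits, the only instrument described is the diary: "The subjects will record their experience on a daily basis in a pain diary". Outcomes has a weekly pain average after each session. Data collection procedure puts a "washout period of 7 days between treatments in order to avoid any residual effects".

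On the expected course of harm, the Background says that the commonest effects "resolve just after the stimuli is terminated", and Technical and scientific resources says that "this treatment has minimal adverse effects".

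**The concern.** Pain is followed for a week after each session, while harm is asked about on the stimulation day only. That timing suits effects that end with the current, which is what the Background expects of the commonest ones. The prompted list is wider: headache, neck pain, a skin reaction, poor concentration or a change of mood can begin or persist after the subject has gone home.

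Two things are at stake. After the third session, a delayed effect has no listed route into the data. Between sessions, a delayed effect can enter the data, but only on a form completed after the next intervention has been given. In a crossover of sham, 1 mA and 2 mA, an effect of one condition may then be counted under another. The trial also informs a later step: under Ethical aspects, all participants are to be offered ten sessions of whichever protocol does best.

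**Working it through.** The plan states no figure on this point, so there is none to reproduce. The check is a comparison of sections, followed by a short calculation.

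**1. Where a delayed effect would be recorded**

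| Effect begins at home after | Next listed enquiry | Position of that enquiry | Rule for attribution |
|---|---|---|---|
| Session 1 (V2) | V3 | After the V3 stimulation | None stated |
| Session 2 (V3) | V4 | After the V4 stimulation | None stated |
| Session 3 (V4) | None | – | – |

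In the first two rows the effect can be reported, because the open-ended question has no recall limit. Nothing says that the past week is to be covered, and the form belongs to a visit at which a different condition has just been applied. In the third row nothing is listed. Because treatment order is randomised, this gap falls on whichever intervention comes last for each subject.

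**2. Window for benefit and window for harm**

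Outcomes needs a weekly pain average after each session, so the diary apparently continues for a week after V4 and has to be collected somehow. No adverse-effect question is attached to it.

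**3. Size of the gap after the third session**

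Inputs: 15 subjects (Sample size), each with one final-session interval, so 15 intervals, one per subject. The rate p of a delayed complaint per interval is an assumption, shown over a range, and subjects are taken as independent.

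Expected unasked events = 15 × p. Chance of at least one = 1 − (1 − p)^15.

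| Assumed p | 15 × p | 1 − (1 − p)^15 |
|---|---|---|
| 5 % | 0.75 | 1 − 0.95^15 = 54 % |
| 10 % | 1.5 | 1 − 0.90^15 = 79 % |
| 20 % | 3 | 1 − 0.80^15 = 96 % |

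**4. What 15 subjects could show with complete enquiry**

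With no events in 15 subjects, the one-sided 95 % upper limit on the true rate is 1 − 0.05^(1/15) = 18.1 %. The two-sided exact limit is 1 − 0.025^(1/15) = 21.8 %. Better timing improves what is recorded, but it does not make this a safety study.

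**The case against.** The strongest reply is that the article does not exclude delayed effects. The open-ended question is phrased in the past tense and has no time limit, and subjects return a week later. A reader might infer that effects between sessions are never asked about. The text does not support that: it neither confines the question to the same day nor says that it reaches back. What stands is that the interval is not specifically sought and that no attribution rule is given.

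A reader might also infer that the trial sets out to conclude that adverse effects are minimal and cannot do so. That is not supported either. The statement is a premise about the technique. Safety is not among the five aims, the outcomes or the dependent variables, and no adverse-effect comparison is specified under Statistical methods. Same-day effects under active and sham stimulation can still be compared.

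A larger magnitude is tempting: all 45 sessions (15 × 3) at 5 % give 2.25 events and 1 − 0.95^45 = 90 %. This counts 30 between-session intervals that the questions at V3 and V4 may cover, and it treats three sessions in one person as independent. It should not be used.

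Nor does it follow that a delayed reaction must stay unknown until the next stimulation. Allocation of interventions allows the list to be opened for a side effect that justifies interruption, and the diary and the pre-stimulation VAS and sensory tests give some information beforehand. None of these is an active enquiry about adverse effects.

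Finally, this is a condensed article, and the full protocol may state a recall period or a follow-up contact. That is a fair limit on any complaint about omission. The point here rests on the timing that the article does fix in three places.

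**Conclusion.** The point holds in a limited form. As published, adverse effects are collected on stimulation days only, after that day's stimulation, and no enquiry is listed after the third session. Effects that begin after that session are not asked about in the published schedule. Effects between sessions may be volunteered, but they are open to misattribution among sham, 1 mA and 2 mA. The tolerability data can be relied on for same-day effects only.

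The firm part of the gap is 15 intervals. Its size in events depends wholly on the assumed 5 % to 20 % rates and on the full protocol adding no later contact. The trial's stated aims and its primary analysis are unaffected. This is a worthwhile, inexpensive improvement to safety ascertainment and not a flaw that undermines the design.

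**What to change.** - At V3 and V4, before stimulation, put the open-ended and itemised questions of Safety monitoring with the wording 'since your last session'. Record the answers against the preceding intervention, on a form separate from that day's questionnaire.
- Keep the present questionnaire after each stimulation for same-day effects.
- Put the same questions once more when the last diary week is collected, and assign the answers to the third session's intervention.
- Tabulate same-day and delayed effects separately by intervention.
- If the full protocol already contains a recall period or a contact after V4, it is enough to state it in Safety monitoring and Table 1.

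The cost is a few minutes at two existing visits and at the final diary collection. No visit, test or change of treatment is added.
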